### Data collection methods

A research assistant will screen for eligibility, solicit consent, and enrol participants. The research assistant will hand an informed consent form to a potential participant in their preferred language and collect baseline characteristics and information on outcomes when applicable.

To minimise loss to follow-up, at enrolment, a geolocation of participants’ place of residence using the ePAL android app, a high-resolution mapping system validated in Blantyre will be used should participants consent. We will also record up to 3 contact phone numbers of the participant and their nominated friends and relatives. Should a participant miss a study visit, we will contact them by phone or by visiting them at home to encourage them to attend the study visit before the expiry of the prescribed visit window.

### Data management

Standardised, pre-tested questionnaires will collect data from participants at every visit. The electronic data collection tools will be designed using REDCap. All paper records will be kept in a locked space and will only be accessible to approved study staff. Furthermore, for the real-time medication monitoring, anonymised data will be stored on a secure server.

Routine data quality assurance processes will be conducted from time to time. Queries will be raised in the database to resolve data recording inconsistencies. In addition, a random sample of individual participant records in the database will be cross-checked with source documents for the correctness of data entry procedures during quality assurance monitoring.

### Statistical analysis

All analyses will be done using R [19]. Reporting will follow the CONSORT guidelines [20]. A flowchart will describe the inclusion and follow-up of participants by study arm. Baseline characteristics and outcomes will be described by the study arm with summary statistics for continuous variables and number and percentage for categorical variables.

The primary and secondary analyses for this study will be the comparison of adherence and viral load suppression proportions between study arms at month 9. A 2-proportion *z*-test will be utilised to test for statistical significance and 95% confidence intervals and *p*-values will be computed. The following analysis sets will be used for both the primary and secondary outcomes:Modified intention-to-treat (mITT): anyone found to be ineligible after randomisation will be excludedPer-protocol (PP) set: this set includes all participants who completed the study without a major protocol deviation

Furthermore, additional analyses of both the primary and secondary outcome will involve the use a logistic regression model adjusted for the pre-specified randomisation stratification factors (sex and age) [21] and important baseline characteristics if found to be unbalanced between study arms [22]. Furthermore, to determine the efficacy of the intervention over time, a multilevel logistic regression model will be utilised. A detailed statistical analysis plan will be submitted later. Lastly, missingness will be defined for important variables, and if appropriate, multiple imputation will be employed. Lastly, no interim analysis is planned, and subgroup analyses will be described in a detailed statistical plan.

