### Sample size

The sample size calculation is an estimation based on ART adherence. At endline, participants will be classified into 2 categories: adherent, and non-adherent based on pill count. The study intends to demonstrate a difference of 15% in adherent participants between the intervention arm (90%) and the control arm (75%). Since there is no recent published literature on baseline adherence levels in YPLHIV in Malawi, virological suppression data from the recent Malawi Population-based HIV Impact Assessment 2020–2021 [13] and an observational study on adherence and virological suppression conducted in the southern districts of Malawi [3] have been used as a proxy for ART adherence in this demographic, hence the 75% expected adherence proportion at endline for the SOC arm. With a power of 80% and *α* = 0.05, we will need 100 participants in each arm. Considering 20% loss-to-follow-up, the sample size needed is 120 participants in each arm. The R statistical package “pwr” version 1.3 was used to compute the sample size [18].

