### Allocation to study arms

For allocation to study arms, stratified block randomisation with variable block sizes will be employed. Allocation cards will be printed and stored in envelopes that will be kept in secure lockable cabinets at the recruitment sites. During the screening/first visit, the research assistant will assign and enrol study participants. The participants’ gender and age will be stratifying factors. The data manager will be responsible for creating allocation cards, while the research assistants will assign participants to each study arm.

Furthermore, it will not be feasible to blind participants and site investigators to arm allocation due to the nature of the intervention. However, for the assessment of the secondary endpoint, laboratory staff processing viral loads will be blinded to arm allocation. Furthermore, the trial statistician will be blinded to study arms when assessing the primary and secondary outcomes.

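### Randomisation is stratified by gender and age, but the primary z-test is unstratified; if those factors predict adherence, the test is mildly conservative (minor, free to improve)

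*Protocol article*

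**What the plan says.** Under Allocation to study arms, the protocol article says that "stratified block randomisation with variable block sizes will be employed" and that participants' "gender and age will be stratifying factors".

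Under Statistical analysis, the primary and secondary analyses compare the proportions adherent and virally suppressed between arms at month 9. A 2-proportion z-test "will be utilised to test for statistical significance and 95% confidence intervals", together with p-values. No stratification or adjustment is attached to that test.

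The same section then says that "additional analyses of both the primary and secondary outcome will involve the use a logistic regression model adjusted for the pre-specified randomisation stratification factors". It lets that model also include baseline characteristics that turn out to differ between the arms.

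Under Sample size, the trial is sized on a difference in proportions: 90% against 75% adherent, 80% power, alpha 0.05, 100 evaluable per arm, raised to 120 per arm for loss to follow-up.

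**The concern.** Stratified blocks hold the arms close to balance on sex and age. If either factor predicts adherence, the difference between the arms then varies less from one randomisation to the next than an unstratified formula assumes. The z-test's variance still counts the between-stratum variation that the design has removed. Its confidence interval is then too wide and its type I error falls below 5%.

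The additional logistic model does not fully make this good. Part of its covariate set depends on what imbalance is seen in the data. It also reports a conditional odds ratio, so the difference in proportions, on which the trial was sized, gets no interval that reflects the stratified design. At stake is a small amount of precision, not the validity of the result.

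**Working it through.** **1. The plan's own figure.** Inputs from Sample size: 75% and 90%, 80% power, alpha 0.05 (taken as two-sided). With the pooled variance and no continuity correction:

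n = [1.96·√(2·0.825·0.175) + 0.8416·√(0.75·0.25 + 0.90·0.10)]² / 0.15² = (1.0532 + 0.4433)² / 0.0225 = 99.5, so 100 per arm.

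This matches the stated figure. Power at 100 per arm by the same formula is 80.2%. The sizing is therefore for an unstratified comparison.

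**2. What has to be assumed.** The article gives no adherence rates by sex or by age within 15–24 years, and no age bands. I assume four equal sex-by-age strata averaging 75%, with a strong spread (60/70/80/90%) and a milder one (65/72/78/85%).

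**3. Share of outcome variance explained by the strata.** R² = Var(stratum rates) / [p(1−p)], with p(1−p) = 0.75·0.25 = 0.1875.

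- Strong: (0.15² + 0.05² + 0.05² + 0.15²)/4 = 0.0125; R² = 0.0125/0.1875 = 0.067.
- Milder: (0.10² + 0.03² + 0.03² + 0.10²)/4 = 0.00545; R² = 0.00545/0.1875 = 0.029.

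**4. Actual type I error.** Under stratified randomisation the unadjusted difference has true variance of about (1−R²) times what the z-test uses. The effective critical value is therefore 1.96/√(1−R²).

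- Strong: 1.96/√0.933 = 2.03; two-sided error about 4.2%.
- Milder: 1.96/√0.971 = 1.99; two-sided error about 4.7%.

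**5. Equivalent loss of sample.** Only the critical value is inflated, because the estimate already has the smaller variance. For 80% power the sample multiplier is [(1.96/√(1−R²) + 0.8416)/(1.96 + 0.8416)]².

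- Strong: (2.870/2.802)² = 1.050, about 5%, or 12 of 240.
- Milder: (2.831/2.802)² = 1.021, about 2%, or 5 of 240.

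These use the control-arm rates for both arms. With the intervention arm at 90% and a common odds ratio, R² falls to 0.055 and 0.024, and the loss to about 4% and 1.7%.

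**6. Power by simulation.** With 100 per arm, the step 2 strata and 200,000 runs, power for the z-test against a Cochran-Mantel-Haenszel test was 82.2% v 83.1% (strong) and 81.9% v 82.1% (milder).

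**7. Wider range.** This used 100,000 runs per scenario, 100 per arm and four equal strata, with overall rates held at 75% and 90%. Type I error is with both arms at 75%.

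| Assumed odds ratio of each factor | Power, unstratified v stratified | Mean 95% CI half-width (points) | Type I error |
|---|---|---|---|
| 1 | 81.6% v 81.3% | 10.26 v 10.31 | 5.0% v 5.0% |
| 1.5 | 81.8% v 81.7% | 10.26 v 10.24 | 4.7% v 4.9% |
| 2 | 82.0% v 82.5% | 10.26 v 10.12 | 4.4% v 4.9% |
| 3 | 82.4% v 84.0% | 10.26 v 9.88 | 3.9% v 5.0% |
| 4 | 83.1% v 85.6% | 10.27 v 9.66 | 3.5% v 5.1% |

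**8. The only prognostic figure in the article.** Background gives viral suppression of 75% in young males and 73.2% in young females, and Sample size uses suppression data as a proxy for adherence. In equal halves the mean is 74.1% and the variance between the sexes is 0.009² = 0.000081. Dividing by 0.741·0.259 = 0.192 gives about 0.04% of the outcome variance. On that figure sex contributes practically nothing, and any real loss would have to come from age.

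**The case against.** The strongest reply is that nothing here is invalid. The estimate is unbiased, the error runs in the safe direction, and the z-test is on the scale used for sizing. Its planned power is kept, and slightly exceeded when the strata are prognostic. A model adjusted for both stratification factors is already pre-specified for both outcomes, so the question is mainly which of two planned analyses carries the primary label. All of that stands, and it limits the point to a minor one. It does not remove it, because the primary interval and p-value still disregard the strata and the planned model does not supply a difference in proportions.

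A reader might infer more in three ways, none of which the document supports.

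- That the intervals are too wide and power is lost as a matter of fact. This needs sex or age to predict adherence within 15–24 years. The article gives no age gradient, and its sex figure points to almost no effect.
- That the loss is 1/(1−0.067) = 1.07, about 7% or 17 of 240. That formula is the gain from adjustment under simple randomisation. Under stratified randomisation the smaller variance is already achieved, and only the critical value is inflated, which gives the 5% above.
- That it is left open which analysis decides. Statistical analysis labels the z-test comparison primary and the logistic model additional, so the order is explicit.

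**Conclusion.** The mismatch between stratified allocation and an unstratified primary test is in the text, and its direction is clear: at worst the test is conservative. Its size depends on stratum rates that the article does not give. Under the two assumed spreads, the type I error is about 4.2% or 4.7% instead of 5%. The loss is equivalent to about 5% or 2% of the sample, with roughly 1 point of power or less. Even at an assumed odds ratio of 4 for each factor, the power difference is about 2.5 points and the intervals are about 6% too wide. If the strata are not prognostic, neither choice loses anything material. False positives are not inflated, and this choice does not breach the planned 80% power. It is a minor point, worth making because the improvement is nearly free.

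**What to change.** For both outcomes, make the primary analysis a risk difference adjusted for the randomisation strata, reported with its 95% CI and p-value. Either a Mantel-Haenszel stratified risk difference, or a logistic regression on arm, sex and age followed by marginal standardisation, would do. Fix the covariates as the stratification factors only. Keep the unadjusted 2-proportion z-test as a sensitivity analysis. Any model that adds covariates for observed imbalance should stay among the additional analyses.

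The cost is rewording. Sex and age must be recorded to randomise, an adjusted model is already planned, and the sample size need not change on this account. If the strata prove not to be prognostic, the price is about 0.3 points of power (81.3% against 81.6%) and a mean interval half-width of 10.31 instead of 10.26 points.

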### Eligibility criteria

The study population will be people living with HIV aged between 15 and 24 years (YPLHIV) on ART registered at the study sites. Participants will be YPLHIV who are non-adherent to ART, i.e. less than 80% of prescribed pill intake based on pharmacy refill counts.

To be included in the study, participants must be on first-line ART regimen (tenofovir/lamuvidine/dolutegravir) or (tenofovir/lamuvidine/efavirenz) according to local guidelines, must have had full disclosure of their HIV status, must be able to read and understand Chichewa or English, and must be competent in the use of mobile devices.

Exclusion criteria include hospitalisation at the time of study entry, prior participation in digital adherence health research, enrolment in other HIV-related studies, and treatment for a comorbidity that significantly increases the participants’ pill burden.

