### Outcomes

The primary outcome is the proportion adherent at 9 months, which is the percentage of prescribed drugs consumed as ascertained on the clinic visit. These will be determined at 1, 2,3, 6, and 9 months. Both self-reported adherence and pharmacy refill counts will be measured at each scheduled visit; these methods have been described in a similar trial by Sumari de Boer et al. [15]. A cut-off of >  = 95% of prescribed pill intake based on the Malawi National Guidelines will be used to classify participants as to whether they were adherent or non-adherent [13].

The secondary outcome is the proportion virologically suppressed at 9 months. A blood plasma sample will be collected for all study participants at baseline and at nine months for viral load testing using real-time polymerase chain reaction (rtPCR). Viral load suppression will be defined by a cut-off of < 200 copies/ml as this cut-off has been shown to have a zero transmission risk and is of public health importance in terms of epidemic control [16, 17].

Serum samples for viral load will be collected by the research assistant or clinic staff. We will follow standard care procedures in obtaining blood samples. These samples will then be sent to the Kamuzu University of Health Sciences Microbiology Laboratory for processing within 24 h.

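### In the additional adjusted analyses, covariates beyond sex and age are chosen by chance imbalance, so baseline viral load will usually be left out

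*Protocol article*

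**What the plan says.** The Statistical analysis section of the protocol article sets out two layers of analysis.

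- **Main comparisons.** Adherence and viral suppression at month 9 are compared between arms without adjustment: "A 2-proportion *z*-test will be utilised to test for statistical significance".
- **Additional analyses.** The article then says that "additional analyses of both the primary and secondary outcome will involve the use a logistic regression model". This model always includes sex and age, which matches the section on allocation: "The participants’ gender and age will be stratifying factors". It also takes in "important baseline characteristics if found to be unbalanced between study arms". The article does not say which characteristics count as important, or by what measure or threshold balance is judged.

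Two baseline quantities bear on the choice. Under Outcomes: "A blood plasma sample will be collected for all study participants at baseline and at nine months for viral load testing". Under Eligibility criteria, entry requires adherence of "less than 80% of prescribed pill intake based on pharmacy refill counts". Neither is named as a covariate. The article also states: "A detailed statistical analysis plan will be submitted later".

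**The concern.** A covariate belongs in an adjusted model because it predicts the outcome. Under randomisation, a difference between arms at baseline is chance and says nothing about prognostic strength. A rule triggered by imbalance therefore has two faults. The content of the model is unknown until the data are seen and would differ from one run of the trial to the next. And a strong predictor that happens to look balanced, as it usually will, is dropped, so most of the benefit of adjustment is lost.

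Baseline viral load is the plain example. Eligibility is set on adherence and not on viral load, so suppressed and unsuppressed participants can both enter. The same measurement nine months later is the secondary outcome. At stake are the precision and credibility of the adjusted results for both outcomes, not the main tests.

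**Working it through.** **1. The plan's own figure.** Inputs from the Sample size section: 90% vs 75%, power 80%, alpha 0.05 (taken as two-sided). With the pooled formula, mean proportion 0.825 and difference 0.15:

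n = [1.960 × √(2 × 0.825 × 0.175) + 0.8416 × √(0.90 × 0.10 + 0.75 × 0.25)]² / 0.15² = (1.0532 + 0.4434)² / 0.0225 = 99.5, so 100 per arm.

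This reproduces the stated 100, with power 80.2%. It is the setting for step 3.

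**2. How often the rule would act.** The article gives no criterion for imbalance, so p<0.05 is assumed. Under randomisation each covariate then triggers in 5% of trials. For k independent covariates, P(at least one enters) = 1 − 0.95^k.

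| Covariates inspected | At least one enters, p<0.05 | At least one enters, p<0.10 |
|---|---|---|
| 1 | 5% | 10% |
| 5 | 23% | 41% |
| 10 | 40% | 65% |
| 15 | 54% | 79% |

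So chance decides whether the model contains anything beyond sex and age, while any particular covariate is absent about 95% of the time (90% at the looser threshold).

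**3. What that costs.** The documents give no association between a baseline covariate and either outcome, so its strength is an assumption, shown over a range. The simulation had 100 per arm, one standard normal covariate, a logistic outcome with marginal rates of 75% vs 90% (75% in both arms for the null), a Wald test at 5%, and 6,000 runs per scenario. Sex and age were not modelled. The conditional strategy adjusts only if a t-test on the covariate gives p<0.05.

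| Log-odds ratio per SD | No adjustment | Adjust only if unbalanced | Always adjust | Loss from the rule |
|---|---|---|---|---|
| 0.5 | 80.6% | 80.6% | 82.0% | 1.4 points |
| 1.0 | 80.2% | 80.6% | 85.3% | 4.6 points |
| 1.5 | 80.5% | 81.6% | 89.0% | 7.4 points |

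The trigger fired in 4.7% to 5.3% of runs. The simulation error of one power figure is about √(0.8 × 0.2 / 6000) = 0.5 points, so the first row is a small effect and the other two are clear. The conditional strategy performs almost like no adjustment.

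**4. Type I error.** Under the null, all three strategies rejected in 4.5% to 5.3% of runs. For one covariate and a fixed trigger, the rule does not inflate the error rate.

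The 75% vs 90% rates are the design values for adherence. The article gives none for suppression, so for that outcome the figures are an illustration.

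**The case against.** **The rule touches only supportive analyses.** This stands. The z-tests use no covariates, so their estimates, intervals and p-values cannot change. A reader might infer that the primary result is exposed to after-the-fact modelling; the article does not support that.

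**Not every covariate depends on imbalance.** This also stands. Sex and age are in the model whatever the data show.

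**A covariate list belongs in the later analysis plan.** In part. Not naming baseline viral load would be no fault by itself. But the article does not leave the choice open: it states a rule, and an analysis plan that followed it would inherit the fault. The trial statistician is to be blinded to arm, which guards against selective choice but does not make chance imbalance a sound criterion.

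**The gain could be put much higher.** A reader might reason from explained variance. With 60% suppressed at entry and 90% vs 50% suppressed at month 9 by entry status, R² = 0.6 × 0.4 × 0.4² / (0.74 × 0.26) = 0.20, and 1/(1 − 0.20) suggests a gain worth 25% more participants; other inputs give 9% to 38%. This does not carry over. The formula is for a linear, risk-difference estimator, whereas the planned model is logistic, where the benefit appears as power. The inputs are also assumed: the Background figures on suppression describe young people with HIV in general, not those below 80% adherence, and nothing gives month-9 suppression by entry status. For the same reason, calling baseline viral load the dominant predictor is an expectation and not a documented fact.

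**Both variables may not be ready to use.** This stands as a caution. The text says the sample is taken at baseline, without placing it before allocation, and assignment happens at the screening or first visit. The schedule table, which may settle this, was not legible in the text reviewed. Refill adherence appears at entry only as an eligibility threshold; the listed adherence assessments are at months 1, 2, 3, 6 and 9. A recorded continuous baseline percentage is an inference.

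**Conclusion.** The point holds for the additional logistic analyses only. Beyond sex and age, the stated rule makes the adjusted model depend on chance and will usually exclude a prognostic baseline value that is collected on everyone. The cost is roughly 1 to 7 percentage points of power in those analyses. That range rests on assumed covariate strengths (log-odds ratio 0.5 to 1.5 per SD), an assumed p<0.05 trigger and the adherence design rates. The documents support neither a larger claim about sample size nor any claim about the main tests. This is a modest fault, worth correcting before the analysis plan is final because it is stated as a rule and is easily removed.

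**What to change.** In the Statistical analysis section, delete the condition on imbalance and name the covariates in advance:

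- **both outcomes:** sex and age, as now;
- **viral suppression:** add baseline viral load, either as log10 or as <200 vs ≥200 copies/ml, with the form chosen now;
- **adherence:** optionally add baseline refill adherence as a continuous percentage, if it is recorded at screening. Its range is cut off at 80%, so its value is uncertain.

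Before adopting viral load, confirm that the baseline sample is drawn before allocation. Baseline characteristics can still be described by arm, but should not decide the model. The cost is wording and one check of the visit procedures; viral load needs no new data. The later analysis plan should carry the same list.
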